### Assignment of interventions: blinding

#### Who will be blinded {17a}

It is not possible to blind the allocated study arm.

#### Procedure for unblinding if needed {17b}

Not applicable, the allocated study arm is not blinded.

### Data collection and management

#### Plans for assessment and collection of outcomes {18a}

The source and timing of measures are summarised in Table 1. The baseline assessment can be done remotely or face-to-face. Participants complete the baseline questionnaire prior to randomisation, with the assistance of their relative, friend or informal carer or research team where required. A catheter urine sample for pH testing will obtained from all participants and tested immediately using the simple urine dipstick test (where participants are recruited without face-to-face contact, the dipstick test and instructions are sent to them by post). Alternatively, a historical urine pH measurement in the 3 months preceding randomisation may be collected from medical records. The local research team completes the baseline CRF.

**Table 1 Tab1:** Source and timing of measures

**Measure**	**Source**	**Randomisation**				
		**Pre**^a^	**Post**			
Catheter blockage requiring intervention	D & CRF		Monthly completion for 24 months			
S-CAUTI requiring antibiotics						
Prophylactic antibiotic use						
Catheter change						
Adverse events						
NHS/healthcare use						
			**Months**			
			**6**	**12**	**18**	**24**
EQ-5D-5L	PQ	**✓**	**✓**	**✓**	**✓**	**✓**
ICIQ-LTCqol	PQ	**✓**	**✓**	**✓**	**✓**	**✓**
GSE Scale	PQ	**✓**	**✓**	**✓**	**✓**	**✓**
ICECAP-A or O	PQ	**✓**	**✓**	**✓**	**✓**	**✓**
Satisfaction with treatment	PQ	**✓**	**✓**	**✓**	**✓**	**✓**
Participant/relative, friend or informal carer’s time and travel	PQ				**✓**	

*CRF* case report form, *D *LTC diary/calendar, *PQ *participant/relative, friend or informal carer-completed questionnaire, *S-CAUTI *symptomatic catheter-associated urinary tract infection, *EQ-5D-5L *EuroQol questionnaire – 5 dimensions – 5 levels, *ICIQ-LTCqol *International Consultation on Incontinence Modular Questionnaire – Long Term Catheter quality of life, *GSE *General Self-Efficacy Scale, *ICECAP-A *ICEpop CAPability measure for Adults, *ICECAP-O* ICEpop CAPability measure for Older people

^a^Pre-randomisation is after informed consent has been given but prior to randomisation

Participants (or the relative, friend or informal carer carrying out the washout or research team) record LTC-related events on their LTC calendar/diary, adapted from a purpose-built diary that has been successfully used in a previous randomised controlled trial in this field [1].

A delegated member of the research team collects the primary outcome, several of the secondary outcomes, adverse events, and adherence approximately monthly for 24 months by telephone or other agreed methods from the participant and/or the relative, friend or informal carer.

Postal or web-based questionnaires are completed by participants with or without assistance from their relative, friend or informal carer or research team at 6, 12, 18, and 24 months after randomisation.

An embedded qualitative component is included to evaluate the participant’s experiences of LTC-related adverse events and their attitudes to, and experiences of, catheter washout (including training). Thirty to 40 participants will be interviewed pre-randomisation and 6–12 months into the study. Participants will be selected using purposive sampling to ensure the diverse characteristics of the population. Approximately twenty health care workers will take part in focus groups 6–12 months into the study to explore attitudes towards washout policies and views on likely outcomes.

#### Plans to promote participant retention and complete follow-up {18b}

Participant retention is promoted by regular monthly contact with the site team to collect outcome measures. Participants receive one reminder to complete each follow-up questionnaire. A small token of appreciation is sent to participants on receiving each completed follow-up questionnaire, unless they opt out on the study consent form. All data collected up to the point of complete withdrawal are retained and used in the analysis. Participants who do not complete their trial follow-up but for whom any outcome data are available are included in the study analysis. If a participant stops using a long-term catheter ≥ 28 days, all data collected up to the point of stopping long-term catheter use are retained and used in the analysis and they are requested to complete an exit questionnaire (EQ-5D-5L only). Deviations from the allocated study arm are recorded in the monthly CRFs and assessed as a secondary outcome measure.

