#### Criteria for discontinuing or modifying allocated interventions {11b}

Washout use is discontinued if a participant stops using the LTC for 28 days or longer, or if they no longer wish to carry out regular washouts, or if they are unable to carry out the washouts following training, or if they withdraw consent for the monthly data collection schedule and decline for this information to be collected less frequently. Where deemed clinically necessary by the clinical team, the pragmatic design of the study permits the following changes to washout policies:An increase in the frequency of LTC washouts, at the onset of the study or following regular review during the course of the studyA change in the type of washout, at the onset of the study or following regular review during the course of the studyThe use of prophylactic washouts in the control arm, following regular review during the course of the study (but not at the onset of the study)

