### Outcomes {12}

The primary clinical outcome is catheter blockage requiring intervention up to 24 months post-randomisation expressed as number per 1000 catheter days.

Intervention is defined as any of the following: unplanned catheter removal or change or washout performed by the participant/designated person or required unplanned visits to/from any healthcare provider, or hospital admission.

The primary economic outcome is the incremental cost per quality-adjusted life year gained for each washout policy compared to standard LTC care only.

Secondary outcomes include:S-CAUTI requiring antibiotics use (as defined by Pickard et al. [15])Duration of LTC in use, catheter change due to other reasons than blockageAdverse events;Hospital admissions, GP/nurse outpatient visits for catheter-related complicationsGeneric quality of life as assessed by EQ-5D-5L [16] (EuroQol Questionnaire – 5 Dimensions – 5 Levels)Condition-specific quality of life assessed by ICIQ-LTCqol [17] (International Consultation on Incontinence Modular Questionnaire – Long Term Catheter quality of life)Adherence to allocated interventionsPatients’ convenience and satisfaction assessed by an adapted version of the abbreviated Treatment Satisfaction Questionnaire for medication [18]Impact on day-to-day activities using the General Self-Efficacy Scale (GSE) [19] and ICECAP-A (ICEpop CAPability measure for Adults) (≤ 65 years) or ICECAP-O [20] (ICEpop CAPability measure for Older people) > 65 yearsTime and travel costs for patients and their relatives, friends or informal carersDiscontinuation of catheter useEvents changing the type and/or frequency (or cessation) of catheter washouts in arms A and B and rates of commencing on prophylactic washouts in arm C

Qualitative study outcomes:Participants’ experience of LTC-related adverse events such as blockage, S-CAUTI, urinary incontinence and bladder pain.Participants’ attitudes/preferences to washout versus no washout policies and expected outcomes (prior to randomisation or knowing their allocated study group) (acceptability).Participants’ experience with washout/no washout policies and evaluation of outcomes (satisfaction).Clinicians’ attitudes towards the influence of washout policies on outcomes.Participants’ and clinicians’ experience of training provided and enactment of the treatment skill. This would clarify the fidelity of the intervention.

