### Sample size {14}

We have used information from a survey of experts and patients and also from available literature to decide that for washouts to be worthwhile there must be a reduction in LTC blockage of 25% [1] (and personal communication, Cambridge PPI group survey). In our case, this would be a reduction in the rate of blockage from 11.8 per 1000 days (unpublished data, [name], [name], 2018) to 8.9 per 1000 days. Participants will be followed up for 2 years. The trial has a 90% power and a significance level of 2.5%. The number of blockages has a negative binomial distribution with a dispersion parameter of 0.6. Recruiting 200 participants per arm allows for approximately 50 out of 730 loss to follow-up days. All available days of follow-up are to be used. The formula from Zhu and Lakkis [21] was used to calculate the sample size for comparing two negative binomial rates.

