### Statistical methods

#### Statistical methods for primary and secondary outcomes {20a}

A statistical analysis plan will document the planned analysis, to be finalised before the data lock. All the main analyses will be based on the intention-to-treat principle. The final analysis will take place after full recruitment and follow-up. Baseline data will be summarised using the appropriate descriptive statistics and graphical summaries. A negative binomial regression of the number of blockages requiring intervention with the log of the number of days catheterised as an offset will be used to analyse the primary outcome. The regression will adjust for the minimisation covariates. A per-protocol analysis will be done as a sensitivity analysis. The appropriate generalised linear model will be chosen for the secondary outcomes and all models will adjust for the minimisation covariates.

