#### Methods in analysis to handle protocol non-adherence and any statistical methods to handle missing data {20c}

Data missing at baseline will be reported as such. If required, missing baseline primary and/or secondary outcome data will be imputed with centre specific mean for continuous data and missing binary/categorical data will include a missing indicator. Multiple imputation methods will be used for missing outcome data.

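### Data collection in effect ends once a participant has been off the catheter for 28 days, so utility, healthcare-use and death data for the trial-based cost per QALY are cut at a post-randomisation event

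*Protocol article*

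**What the plan says.** All references are to the protocol article.

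- **Retention, {18b}.** When a participant stops using a long-term catheter for 28 days or more, "all data collected up to the point of stopping long-term catheter use are retained and used in the analysis". The same section uses a parallel formula for complete withdrawal: what was gathered until then is kept and analysed. For people who stop the catheter, one last form follows: "they are requested to complete an exit questionnaire (EQ-5D-5L only".
- **Discontinuing interventions, {11b}.** "Washout use is discontinued if a participant stops using the LTC for 28 days or longer". This rule concerns the treatment. It does not say that follow-up stops.
- **Outcome collection, {18a} and Table 1.** Blockages, adverse events and NHS/healthcare use are collected monthly for 24 months, and questionnaires "at 6, 12, 18, and 24 months after randomisation". No exception is made for people who stop.
- **Outcomes, {12}.** "The primary economic outcome is the incremental cost per quality-adjusted life year gained for each washout policy compared to standard LTC care only". Discontinuation of catheter use is a listed secondary outcome.
- **Additional analyses, {20b}.** The economic evaluation has a trial-based analysis and a lifetime model.
- **Statistical methods, {20a}.** "All the main analyses will be based on the intention-to-treat principle". The primary model uses log days catheterised as its offset.
- **Missing data, {20c}.** "Multiple imputation methods will be used for missing outcome data".
- **Harms, {22}.** SAEs are recorded until the last trial follow-up. They are limited to serious events related to the catheter or washout procedure, plus all deaths.

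**The concern.** Stopping the catheter happens after randomisation. Blockage or infection could plausibly prompt it, so its frequency may depend on the allocated arm. Section {18b} handles it much as it handles withdrawal from the study.

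For a rate per catheter day that is acceptable. For a cost per QALY it is not, because a person's utility, healthcare use and survival still count after the catheter is out. The exit form gives one utility reading and no resource use. A later death would not be seen if contact has ended.

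If washouts change how often catheters are stopped, the unobserved time differs by arm and the cost and QALY differences can be biased. Missing values for people who stopped would have to be filled with very little off-catheter information. Costs are exposed too: the Background describes weekly bag or valve changes and catheter changes every 4–12 weeks, which people without a catheter no longer need.

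**Working it through.** **1. Does the text end collection?** It does not say so in words. But {18b} keeps data up to stopping, repeats the formula used for withdrawal, calls the last form an exit form, restricts it to one instrument, and describes no later contact. Set beside the unqualified 24-month schedule in {18a}, the two sections need reconciling.

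**2. Effect on the primary clinical outcome.** The plan's own figure is 200 per arm. Inputs from {14}: rates r0 = 0.0118 and r1 = 0.0089 per day, dispersion k = 0.6, t = 730 − 50 = 680 days, 90% power, 2.5% level.

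- V = (1/t)(1/r0 + 1/r1) + 2k = (84.75 + 112.36)/680 + 1.2 = 1.490
- n = (1.960 + 1.282)² × V / [ln(r1/r0)]² = 10.507 × 1.490 / 0.07955 ≈ 197 per arm

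This matches 200 with 2.5% taken as one-sided; the article does not state sidedness. With 200 per arm, power is 90.8% at 730 days and 89.7% at 600 days. At two-sided 2.5% it goes from 85.3% at 730 days to 84.0% with 30% stopping (614 days). Either way, stopping costs about one percentage point. Most of that would be lost under any collection rule, because uncatheterised days carry no exposure.

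**3. Unobserved time for costs and QALYs.** The documents give no stopping rate, so every rate here is an assumption.

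*Stopping midway on average:* each person who stops loses 1 of 2 years. Per arm there are 200 × 2 = 400 person-years.

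- 5%: 200 × 0.05 × 1 = 10 person-years, 10/400 = 2.5%
- 15%: 200 × 0.15 × 1 = 30 person-years, 30/400 = 7.5%

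*Constant hazard:* h = −ln(1 − p)/730, and mean days lost = 730 − p/h.

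| Stopping by 24 months (p) | Mean days lost per randomised person | Share of 730 |
|---|---|---|
| 5% | 18.4 | 2.5% |
| 10% | 37.1 | 5.1% |
| 15% | 56.2 | 7.7% |
| 20% | 75.7 | 10.4% |
| 30% | 116.0 | 15.9% |

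The two approaches agree over 5–15%.

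**4. Possible QALY shift.** Assume that utility off the catheter differs by 0.1 from that on it, and that the gap is filled entirely with on-catheter values.

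- Stopping differs by 5 percentage points, 1 year lost each: 0.05 × 1 × 0.1 = 0.005 QALY per randomised person.
- Stopping 10% versus 20%: (75.7 − 37.1)/365 = 0.106 years; 0.106 × 0.1 ≈ 0.011 QALY.

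Both figures give the exit EQ-5D-5L no weight. To the extent that it anchors later utilities correctly, the shift falls towards zero. No cost shift can be computed, because the article gives no unit costs.

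**The case against.** The strongest reply is that a condensed article may leave handling after cessation to the full protocol, and the imputation model to an analysis plan that is not shown. The exit EQ-5D-5L is tied to 28 days or more off the catheter, so it plausibly measures the off-catheter state. The lifetime model means the economic result does not rest on trial follow-up alone. The cost-per-QALY outcome names no horizon, and intention to treat is an analysis principle, not a collection schedule. Eligibility requires no plan to discontinue, and the Background cites a mean catheter duration of six years, so stopping may be uncommon.

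Much of this limits the size. It does not remove the point, because {18b} states a rule and does not merely leave something out. The exit form collects no resource use, and imputation cannot fully replace data that the rule stops collecting.

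Four stronger readings are tempting but unsupported:

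- **People who restart a catheter are lost.** The article says nothing on re-entry, in either direction.
- **The rule contradicts the sample-size section.** That section says "All available days of follow-up are to be used", but days never collected are not available days, so nothing is contradicted.
- **Safety data in general are lost.** Given the SAE definition in {22}, the loss is mainly later deaths and a few late related events.
- **The primary blockage comparison is undermined.** Its offset is days catheterised, so it is little affected.

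**Conclusion.** The point holds for the economic evaluation. In effect, {18b} truncates EQ-5D-5L, healthcare use and deaths at a post-randomisation event that may differ by arm and is a listed outcome. That does not fit the 24-month schedule, intention to treat or a trial-based cost per QALY.

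The conclusion rests on reading {18b} as ending collection, which is a strong inference and not an explicit statement. The magnitude rests wholly on assumptions about the stopping rate, its timing, the difference between arms and the utility gap. On those, the bias is probably small and would matter only if the true QALY difference is also small. The case for change is that the remedy is cheap and data not collected cannot be recovered at analysis.

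**What to change.** Amend {18b} to say three things:

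1. A participant who stops catheter use contributes no catheter-days while uncatheterised.
2. EQ-5D-5L, healthcare use, deaths and any SAEs within the {22} definition continue to be collected at the scheduled times to 24 months, unless consent is withdrawn.
3. If a long-term catheter is re-inserted within 24 months, catheter-days and blockages are again recorded and analysed as randomised. This concerns data collection only and says nothing on restarting washouts.

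The cost is a protocol amendment with the approvals listed in {25}. It uses at most the four existing follow-up questionnaires per person and the existing remote contacts, for what is likely to be a small number of people. The downside is a small extra burden on participants who no longer have a catheter.

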#### Data management {19}

Local study team members as listed on the delegation log can enter locally collected data. Safety data, CRFs and participant questionnaires are entered into the study website. Questionnaires returned by post to the trial office are entered there. The staff in the trial office work closely with local study teams to ensure the data is as complete and accurate as possible. The quality of data is enhanced by extensive range and consistency checks. Databases are backed up onto hard disc at an offsite location. All CRF and questionnaire keystrokes are recorded to maintain a full audit trail. All essential data and documents are retained for a period of at least 10 years after close of trial.

#### Confidentiality {27}

Data is stored on a secure database under the current Data Protection Legislation (General Data Protection Regulation and the Data Protection Act 2018). Personal data is not kept for longer than is necessary for the purpose for which it is processed. Access rights to the data set is managed.

#### Plans for collection, laboratory evaluation and storage of biological specimens for genetic or molecular analysis in this trial/future use {33}

Not applicable, no samples collected.

### Statistical methods

#### Statistical methods for primary and secondary outcomes {20a}

A statistical analysis plan will document the planned analysis, to be finalised before the data lock. All the main analyses will be based on the intention-to-treat principle. The final analysis will take place after full recruitment and follow-up. Baseline data will be summarised using the appropriate descriptive statistics and graphical summaries. A negative binomial regression of the number of blockages requiring intervention with the log of the number of days catheterised as an offset will be used to analyse the primary outcome. The regression will adjust for the minimisation covariates. A per-protocol analysis will be done as a sensitivity analysis. The appropriate generalised linear model will be chosen for the secondary outcomes and all models will adjust for the minimisation covariates.

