### Assignment of interventions: allocation

#### Sequence generation {16a}

Participants are allocated 1:1:1 to one of the three trial arms by a member of the local research team using a centralised computerised randomisation system (administered by the Centre for Healthcare Randomised Trials (CHaRT), University of Aberdeen. Random allocation uses the minimisation covariates: region; gender; age (< 45 years, 45–64 years and ≥ 65 years); residential status (care home vs community); previous blockages requiring intervention in the last 6 months (0 vs ≥ 1); previous S-CAUTI requiring antibiotics in last 6 months (0 vs ≥ 1); Urine pH (normal vs acidic vs alkaline vs not available).

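### The primary model uses prior blockage only as 0 versus ≥1; adding the baseline count would gain precision, by an amount that depends on a correlation the protocol does not give

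*Protocol article*

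**What the plan says.** The statistical methods section (20a) specifies "A negative binomial regression of the number of blockages requiring intervention with the log of the number of days catheterised as an offset" and then states that "The regression will adjust for the minimisation covariates". It names no further covariate for the primary outcome. It refers to a statistical analysis plan, to be finalised before data lock, which is not at hand.

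The sequence generation section (16a) lists the minimisation covariates. The one for earlier blockage is "previous blockages requiring intervention in the last 6 months (0 vs ≥ 1"), a two-level factor.

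The sample size section (14) plans "a reduction in the rate of blockage from 11.8 per 1000 days" "to 8.9 per 1000 days", with 200 participants per arm, about 680 of 730 days observed, 90% power and a significance level of 2.5%. It also states: "The number of blockages has a negative binomial distribution with a dispersion parameter of 0.6".

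No section says whether the number of blockages before randomisation is recorded at baseline. The planned subgroups (20b) separate participants with no history of blockage from those with recurrent blockages. That suggests more than a yes/no answer may be held, but does not establish it.

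**The concern.** The outcome is a count of blockages per patient. The natural baseline predictor of that count is the patient's own earlier count of the same event. A two-level split suits minimisation, but as the only form of this covariate in the analysis it discards the difference between an occasional and a frequent blocker.

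Most of the planned variance comes from differences between patients, which is the component a baseline count can partly explain. The same model carries both primary comparisons (saline versus control and acidic versus control), so any precision given up is given up twice.

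**Working it through.** **Inputs from the protocol article.** Control rate 0.0118 per day; intervention rate 0.0089 per day; follow-up 730 − 50 = 680 days; 200 per arm; level 2.5% (sidedness not stated); dispersion k = 0.6, read as variance = μ + kμ².

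**Assumption.** The correlation between a patient's blockage rate in the 6 months before randomisation and during follow-up is not given. It is varied from 0.3 to 1.0.

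**Step 1: the plan's own figure.** Per-patient variance of the log rate ratio:

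V = (1/0.0118 + 1/0.0089)/680 + 2 × 0.6 = 0.29 + 1.20 = 1.49

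ln(0.0089/0.0118) = −0.282

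n = (z_α + z_β)² × V / 0.282²

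- 2.5% one-sided: (1.960 + 1.282)² × 1.49 / 0.0796 ≈ 197 per arm, which matches the planned 200; power at 200 is 90.5%.
- 2.5% two-sided: (2.241 + 1.282)² × 1.49 / 0.0796 ≈ 232 per arm; unadjusted power at 200 is about 85%.

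Between-patient dispersion contributes 1.20/1.49 ≈ 81% of V.

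**Step 2: what the split discards.** Expected blockages in 6 months: 0.0118 × 182.5 = 2.15. Under the negative binomial, P(0) = (1 + 0.6 × 2.15)^(−1/0.6) = 0.25. About 75% of participants would therefore share the ≥1 category.

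**Step 3: gain from adding the count.** Trials of 200 versus 200 were simulated with gamma-distributed patient rates, linked before and after randomisation by a Gaussian copula. The baseline count covers 182.5 days and follow-up 680 days. Negative binomial models were fitted by maximum likelihood with 0/≥1 alone, then with 0/≥1 plus log(1 + count). There were 3000 replicates per row and Monte Carlo error of about 0.5 point. The other minimisation covariates were not simulated.

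| Correlation | Residual k | Standard error | Power, 2.5% one-sided | Power, 2.5% two-sided |
|---|---|---|---|---|
| 1.0 | 0.44 → 0.27 | 0.0779 → 0.0666 | 95.1 → 98.8% | 91.6 → 97.7% |
| 0.7 | 0.52 → 0.44 | 0.0823 → 0.0780 | 92.2 → 94.6% | 87.6 → 90.6% |
| 0.5 | 0.56 → 0.52 | 0.0843 → 0.0823 | 91.1 → 92.2% | 85.2 → 87.0% |
| 0.3 | 0.58 → 0.57 | 0.0855 → 0.0848 | 89.8 → 90.2% | 84.6 → 84.8% |

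The standard error falls by 1 − 0.0666/0.0779 = 14.5%, then 5.2%, 2.4% and 0.8% down the rows. Further runs at the intermediate values 0.8 and 0.6 gave falls of about 7% and 4%.

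**Step 4: larger dispersion.** The background section (6a) cites a cohort in which 34% of patients blocked over 12 months, at 8.54 per 1000 days. With full-year exposure the mean is 3.12, and solving (1 + 3.12k)^(−1/k) = 0.66 gives k ≈ 7.8. One-sided power then moves from 37.5% to 61.6% at correlation 1.0, but only from 23.0% to 23.7% at 0.7 and from 19.7% to 20.0% at 0.5. Here the adjusted models' standard errors fall below the empirical spread of the estimates, so these powers are optimistic. The large gain at high k also needs near-perfect stability.

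**The case against.** The stated model is standard and agrees with the randomisation section; nothing in the document contradicts itself here. Extra prognostic covariates are often left to the analysis plan, which may already include the count. That stands, and it limits the point to an improvement rather than an error. The article does name the covariate set, however, and the only form of prior blockage it names is the split.

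The gain rests on an unreported correlation. Perfect stability is doubtful: section 11b permits washout policy to change during the study, including prophylactic washouts in controls, and section 6a describes more frequent catheter changes as the usual response to blockage. This also stands, which is why the size is given as a range.

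Two stronger readings are tempting.

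- A reader might infer that the count would recover much of the power lost to between-patient variation. At k = 0.6 and the one-sided level, the shortfall from 100% remaining after the split goes from 4.9 to 1.2 points at correlation 1.0, about three quarters recovered. At 0.7 it goes from 7.8 to 5.4 (about 31%), and at 0.3 from 10.2 to 9.8 (about 4%). No figure in the document supports the top of that range.
- A reader might infer that the trial is already below its stated power. The 200 per arm is reproduced at 2.5% one-sided, with k = 0.6 already built in. A shortfall appears if 2.5% is two-sided and the analysis explains little of the variation, or if k is larger. Those are separate questions.

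**Conclusion.** The point holds in a limited form. The only stated adjustment for prior blockage is 0 versus ≥1, and at the planning inputs that places about three quarters of participants in one category. A prespecified count term would give some precision on both primary comparisons and keep the minimisation factors.

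At k = 0.6 and 200 per arm, the standard error falls by about 15% at best and about 1% at a correlation of 0.3. Power rises by about 4 points one-sided, or 5 to 6 two-sided, at best, and by almost nothing at the low end. This assumes gamma-distributed patient rates and an accurately reported baseline count; recall error would reduce the gain, and so would a planning value of 0.6 that already reflects covariate adjustment.

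**What to change.** Before data lock, and without reference to outcomes by arm, specify the primary negative binomial model with treatment, the minimisation factors (including the 0/≥1 term) and log(1 + number of blockages requiring intervention in the 6 months before randomisation), where that number is recorded at baseline.

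If the baseline form holds only the dichotomy, record the number for later participants and state a rule for the rest. One workable rule is to keep the 0/≥1 term, set the count term to a constant and add an indicator for count not recorded. Participants in the 0 group have a known count of zero, so only the ≥1 group needs this. The rule has to be written out because section 20c assigns the missing indicator to binary and categorical baseline data and a centre mean to continuous data, and does not clearly cover a count missing for early recruits.

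The cost is analysis-plan wording if the number is already held. Otherwise it includes a small mid-trial change to the baseline form, since recruitment began in December 2019, and a smaller gain because early recruits contribute only the dichotomy.
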